## Results

### Sample Size and Participant Flow

Based on previous studies of gait analysis using HAL, we calculated the required sample size using JMP (version 12; SAS Institute), assuming a 1.5-fold improvement in the 6MWD. With an alpha of .05, a power of 0.8, and an effect size of 0.8, the calculated sample size was 20. Considering potential dropouts, we set the final target sample size at 20 participants. The overall flow of the trial, including participant recruitment, consent, evaluation, surgery, intervention, and 6-month follow-up, is planned in accordance with the SPIRIT 2013 statement.

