**Results:**

The planned sample size is 20 patients, calculated using JMP version 12 (SAS Institute) based on an expected 1.5-fold improvement in 6-minute walk distance (effect size 0.8, α=.05, power=0.8). Analyses will be performed using SPSS version 15.0 (IBM Corp). The 2-minute walk test (primary outcome) and secondary outcomes will be compared at baseline, post intervention, and 6-month follow-up using 1-way analysis of variance or Kruskal-Wallis test, and *P* values <.05 and 95% CIs will be reported.

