### Sample Size

The calculation was performed with α=.05, a statistical power of 0.8 (80%), and an effect size of 0.8, resulting in a total sample size of 20. The target sample size includes a margin to accommodate potential dropouts. However, if the number of dropouts significantly impacts statistical power or data integrity, we plan to recruit additional participants to maintain the robustness of the analysis.

The sample size will be estimated using data from the 6-minute walk distance (6MWD), as sufficient effect size data for this outcome are available in the literature, and it is a widely recognized measure of functional walking capacity in rehabilitation research. However, performing the full 6MWD may be overly demanding for patients in the early postoperative period following limb amputation; therefore, the 2-minute walk distance (2MWD) will be selected as the primary end point. The 2MWD has been validated as a reliable and less physically demanding alternative to the 6MWD, with strong correlations reported between the two measures in neuromuscular and rehabilitation populations [13,15].

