### Statistical Analysis

The target sample size was set at 20 patients scheduled for lower limb amputation. Using JMP version 12 (SAS Institute), the sample size was calculated based on a research design assuming that the 6MWD would improve by a factor of 1.5, referencing previous studies on gait analysis using the HAL [16]. The calculation was performed with α=.05, power=0.80, and a prespecified effect size.

The primary analysis population for efficacy evaluation will be the Full Analysis Set (FAS), whereas the secondary analysis population will be the Per Protocol Set (PPS).

The FAS includes all study participants who have undergone at least one session of HAL-assisted gait training and have had at least one efficacy-related observation thereafter. However, individuals who fail to meet the eligibility criteria will be excluded. The PPS comprises participants from the FAS who have completed HAL-assisted gait training (5 days per week, 30 minutes per day) without major deviations from the study protocol and for whom the primary evaluation item can be assessed.

Statistical analyses will be conducted using SPSS version 30.0 (IBM Corp). The primary evaluation item, the 2-minute walking distance, will be analyzed using the FAS population, and the mean (SD) [or median (minimum-maximum)] will be calculated. Comparisons between preoperative, postintervention, and 6-month postoperative outcomes will be performed using a 1-way ANOVA or the Kruskal-Wallis test, with a 2-sided significance level of 5%, and a 95% CI will be calculated. In addition, the same analysis will be performed using the PPS as a secondary approach.

For secondary evaluation items, analysis will also be conducted using the FAS population. The mean (SD) [or median (minimum-maximum)] will be calculated for bilateral lower limb muscle strength, skeletal muscle mass, sensory impairment, range of motion, Berg Balance Scale, timed up and go test, gait parameters (step length, stride length, weight distribution, and gait speed during the 10-minute walk test), maximal oxygen uptake, and Locomo 25. Comparisons between preoperative, postintervention, and 6-month postoperative outcomes will be performed using a 1-way ANOVA or the Kruskal-Wallis test, and multiple comparisons will be conducted using the Tukey method (or Steel-Dwass test). A 2-sided significance level of 5% and a 95% CI will be used. The same analysis will also be performed using the PPS as a secondary approach.

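### The figure of 20 is given both as the calculated sample size and as a target that includes a dropout margin, and a paired test on the stated inputs gives 15, not 20

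*Protocol article*

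**What the plan says.** The sample size is described in four places: the Results paragraph of the Abstract, Sample Size and Statistical Analysis in the Methods, and Sample Size and Participant Flow in the Results.

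- **Inputs.** The Abstract gives "effect size 0.8, α=.05, power=0.8", and the Methods repeat "a statistical power of 0.8 (80%), and an effect size of 0.8". Statistical Analysis adds that the calculation rests on "assuming that the 6MWD would improve by a factor of 1.5".
- **Result.** Sample Size and Participant Flow says: "With an alpha of .05, a power of 0.8, and an effect size of 0.8, the calculated sample size was 20". Sample Size in the Methods likewise presents 20 as the output of the calculation.
- **Dropouts.** Sample Size in the Methods says: "The target sample size includes a margin to accommodate potential dropouts". Sample Size and Participant Flow says: "Considering potential dropouts, we set the final target sample size at 20 participants". No dropout rate is given.
- **Additional recruitment.** If dropouts significantly affect power or data integrity, "we plan to recruit additional participants to maintain the robustness of the analysis". No number defines when this applies.
- **Test.** None is named for the sample size calculation, and the type of effect size is not given. The planned analysis is a one-way ANOVA or Kruskal-Wallis test over three time points, "with a 2-sided significance level of 5%, and a 95% CI will be calculated".

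**The concern.** A calculated number and an enrolment target that allows for losses are different quantities. The target exceeds the calculated number by whatever the dropout rate requires. Here both are 20, in two separate sections, so either the margin does not exist or 20 was not what the calculation produced.

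The inputs do not settle which. Each patient is measured repeatedly in a single arm, and the primary assessment is at 8 weeks, so the natural calculation is a within-patient comparison. That gives a number well below 20.

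What is at stake is the number of evaluable patients the trial needs. If it is 15, enrolling 20 leaves room for five losses. If it is 20, the first loss takes the trial below its requirement. The additional-recruitment sentence depends on the same number, so as written nobody can say when it should take effect.

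**Working it through.** **Inputs.** Alpha 0.05, power 0.80 and effect size 0.8 come from the Abstract and both sample size sections. Two-sided testing comes from Statistical Analysis, where it is stated for the analysis; it is assumed here for the sample size too. The single arm with repeated measurement comes from the Abstract.

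**1. Attempt to reproduce 20: paired t-test.** Let the effect size be the mean change divided by the SD of the change, dz = 0.8. With n patients, df = n − 1 and the noncentrality is dz × √n. Power is the probability that a noncentral t exceeds the two-sided 5% critical value in absolute size.

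| n | noncentrality 0.8√n | critical t | power |
|---|---|---|---|
| 14 | 2.993 | 2.160 | 0.790 |
| 15 | 3.098 | 2.145 | 0.821 |
| 20 | 3.578 | 2.093 | 0.924 |

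The smallest n reaching 0.80 is 15. The stated 20 is not reproduced; with 20 evaluable patients the power is 0.92.

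**2. Other readings of the same inputs.**

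- Paired t-test, one-sided: 12.
- Wilcoxon signed-rank, dividing 15 by an efficiency of 0.955 or 0.864: 15.7 or 17.4, so 16 to 18.
- Two-sample t-test, two-sided: 26 per group. This does not fit a single arm.
- One-way ANOVA with three independent groups and 0.8 read as Cohen's f: 19 in total (power 0.816), or 21 if balanced at 7 per group; a total of 20 gives 0.841. This total counts independent subjects. With three measurements per patient it corresponds to about 7 patients.

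**3. Routes that give exactly 20 patients.** Each needs an ingredient that the article does not state.

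- 0.8 is a difference between time points in units of the between-patient SD, with correlation ρ = 0.3. Then dz = 0.8/√(2(1 − ρ)) = 0.8/√1.4 = 0.676, and n = 20 (power 0.818; 19 gives 0.796).
- Alpha is divided by three for three contrasts (0.05/3), with dz = 0.8: n = 20 (power 0.818; 19 gives 0.791).
- 15 evaluable patients with 25% loss: 15/(1 − 0.25) = 20.

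**4. The dropout statements.** If 20 is the calculated number, 20 − 20 = 0 is left for losses. A real margin on 20 evaluable patients would mean enrolling:

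- 20/0.90 = 22.2, so 23, at 10% loss;
- 20/0.80 = 25 at 20% loss;
- 20/0.75 = 26.7, so 27, at 25% loss.

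These rates are assumptions. If 15 is the calculated number, the margin is 5 of 20, or 25%. That agrees with the margin sentence in the Methods but not with the statement that 20 was the calculated size.

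**The case against.** The strongest reply is that 20 cannot be called wrong when neither the test nor the effect-size type is known. This stands. A reader might infer that no calculation on these inputs yields 20, and step 3 shows otherwise. An ANOVA with f = 0.8, from the test family the article names, also comes close at 19, although that total does not count patients measured three times. The supportable statement is that 20 cannot be verified as written and differs from the result of the natural paired calculation.

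Four stronger readings are tempting, and the article does not support them.

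- **That the trial is underpowered.** On the paired reading, 15 evaluable patients give 0.82 and 20 give 0.92. Treating the three time points as independent groups yields lower powers, but the same patients are measured each time, so those are not the powers of this design. The choice of an independent-groups test is a separate matter.
- **That the effect size has no basis.** The 1.5-fold assumption is referred to earlier HAL work. The SD and the conversion to 0.8 are details that a journal article may leave to the full protocol.
- **That the top-up rule inflates the type I error.** The stated trigger is dropouts, not a non-significant result, and no interim look at efficacy is described. The trigger is vague, but a result-driven extension is not what the article sets out.
- **That the sponsor meant 15 patients plus 25% loss.** This is one way to reconcile the text, but neither figure is printed.

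The reply does not touch the dropout contradiction. Both statements are printed, so it is not a detail left to a fuller document.

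**Conclusion.** The point holds in two parts.

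First, the article contradicts itself: 20 cannot be both the direct output of the calculation and a target containing a dropout margin, because the margin is then zero. This needs no assumption beyond the text.

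Second, 20 is not reproduced on the natural reading. A two-sided paired t-test with a standardised change of 0.8 needs 15 evaluable patients, five fewer than stated, and 20 evaluable give 0.92 power where the article states 0.80. This part assumes two-sided testing and that 0.8 is the mean change over its SD. If 0.8 is instead a between-patient standardised difference, the required number depends on the correlation: 27, 22, 20 and 15 at correlations of 0, 0.2, 0.3 and 0.5.

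The fault is therefore an inconsistent, unverifiable figure. On the paired reading it is not a shortage of patients. It should still be corrected, because the number of evaluable patients required, and with it the point at which additional recruitment is due, cannot be read from the article.

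**What to change.** Make the following changes in the Results paragraph of the Abstract, in Sample Size and Statistical Analysis in the Methods, and in Sample Size and Participant Flow in the Results.

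1. State the test, the sidedness and the type of effect size actually used in the calculation.
2. Give the evaluable number and the enrolled number separately, with the assumed dropout rate.
3. Reconcile the two dropout statements according to what was done:
   - If the calculation was paired with a standardised change of 0.8, write that 15 evaluable patients give 82% power and that enrolling 20 allows up to 25% loss. Delete the statement that the calculated size was 20.
   - If 20 is the evaluable number, name the ingredient that produces it and withdraw the claim that 20 includes a dropout margin.
4. Tie the additional-recruitment sentence to a count: it applies when the number of evaluable week-8 2-minute walk distances falls below the stated evaluable number, decided without reference to outcome results.

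The sponsor must say which branch of item 3 applies; it cannot be inferred from the article. The cost is rewording in four places. Enrolment stays at 20.

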### Planned Outcomes and Statistical Analysis

For the primary outcome, the 2MWD, we will compare results at 3 time points: preoperative, post intervention, and 6-month follow-up. Data will be presented as mean (SD) [or median (minimum-maximum)]. Comparisons will be performed using a 1-way ANOVA or the Kruskal-Wallis test, with a *P* value <.05 and 95% CIs reported.

Secondary outcomes will be analyzed using a similar approach. Descriptive statistics will be calculated for objective measures, like muscle strength, balance, and gait parameters, as well as for subjective scales including ADL/QOL assessments (BI, FIM, and FAI). Multiple comparisons will be conducted using the Tukey method or the Steel-Dwass test, with a *P* value <.05 and 95% CIs also reported.

For missing data, we will first conduct a descriptive analysis to assess the pattern of missingness. If the data are judged to be missing at random, multiple imputation will be applied to the primary outcomes. Sensitivity analyses will also be performed by comparing results from complete-case and imputed datasets to assess the robustness of the findings.

The primary efficacy analysis will be conducted on the FAS, and a secondary analysis on the PPS.

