### Outcomes

All gait evaluations at 2 weeks, 8 weeks, and 6 months postoperatively will be conducted without the use of the HAL device. For the primary outcome, assessment will be conducted at 8 weeks postoperatively to evaluate the short-term effectiveness of early HAL-assisted gait training, which is expected to influence the critical period of initial rehabilitation and prosthetic adaptation. Functional recovery may continue beyond this period, particularly up to 6 months; however, the 8-week period was chosen as the primary end point to capture the immediate impact of the intervention. A 6-month follow-up will provide important secondary data on longer-term outcomes. At each time point, walking ability will be assessed under standard conditions using the residual limb or temporary prosthesis, as applicable. A comprehensive examination of various walking-related factors is necessary; therefore, we will collect the items listed in Table 1 extensively. Among these evaluation items, the 2-minute walking distance [13,14] is set as the primary evaluation item, as it is a general indicator of walking ability and is directly linked to ADL and QOL. Other items will be collected as secondary evaluation items. The Locomo 25 is an assessment tool used to evaluate the condition of locomotive syndrome, which indicates a decline in mobility [15].

**Table 1 table1:** Primary and secondary outcomes.

Assessment item			Description

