The 6-month follow-up assessment may be less sensitive in detecting differences attributable to early intervention timing; however, it is intended as a final confirmation of functional walking status. The primary outcome, however, is the 2MWD measured immediately after the 8-week intervention period, which directly reflects the effect of early HAL-assisted rehabilitation. We acknowledge that a 6-month follow-up period may not capture the full extent of functional recovery, particularly for transfemoral amputees. In particular, longer-term adaptations such as neuromuscular reorganization, prosthetic control proficiency, and reintegration into daily activities may require extended periods to fully manifest. While this duration allows for the assessment of short- to midterm effects of early intervention, the decision to limit follow-up to 6 months balances practical feasibility, participant burden, and the exploratory nature of this protocol. Future studies should consider longer follow-up periods to evaluate sustained outcomes and late-phase rehabilitation progress.

Another limitation is the strict eligibility criteria required for HAL use, including specific height, weight, and residual limb conditions. These requirements may exclude certain patient populations, which could limit the generalizability of the findings. Nevertheless, these criteria are necessary to ensure patient safety and to accommodate the technical specifications of the HAL system.

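### The primary endpoint is the week-8 2-minute walk distance, but the only primary test stated is an omnibus comparison that includes month 6 and names no week-8 contrast

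*Protocol article*

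**What the plan says.** **Endpoint.** Under Outcomes, "the 8-week period was chosen as the primary end point to capture the immediate impact of the intervention", and of the later visit, "A 6-month follow-up will provide important secondary data on longer-term outcomes". Limitations repeats it: "The primary outcome, however, is the 2MWD measured immediately after the 8-week intervention period". HAL training runs to postoperative week 8 (Interventions), so the postintervention time in the analysis text is week 8.

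**Primary test.** Planned Outcomes and Statistical Analysis says "For the primary outcome, the 2MWD, we will compare results at 3 time points: preoperative, post intervention, and 6-month follow-up", and then "Comparisons will be performed using a 1-way ANOVA or the Kruskal-Wallis test". The Statistical Analysis section and the Results part of the Abstract give the same three-time comparison. Statistical Analysis adds the error level: "with a 2-sided significance level of 5%, and a 95% CI will be calculated". It does not say which quantity the interval is for.

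**Pairwise comparisons.** "Multiple comparisons will be conducted using the Tukey method or the Steel-Dwass test" stands in the paragraph on secondary outcomes. In Statistical Analysis, too, the Tukey and Steel-Dwass procedures are attached only to secondary items. The paragraph on the primary item has none.

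**Sample size.** The inputs are "α=.05, a statistical power of 0.8 (80%), and an effect size of 0.8", giving 20 patients. Neither the test nor the type of effect size is named.

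**The concern.** An omnibus test over three times asks whether the means differ anywhere among preoperative, week 8 and month 6. The endpoint asks whether walking distance at week 8 differs from the preoperative value. The first can be answered yes when the answer to the second is no.

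Month 6 falls about four months after HAL training ends, and the schedule in Table 2 shows prosthesis gait training continuing to that visit. A difference at month 6 is therefore easy to imagine whatever happened by week 8. If it drives the omnibus P value, the one inferential result given for the primary outcome carries no specific information on the time that the article chose as primary.

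The contrast should also be fixed before the data are seen. If it is picked after a significant omnibus result, the choice is data-driven.

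**Working it through.** **1. Inputs.** From the article: n = 20, single arm, the same patients at three times, two-sided 5%, 1-way ANOVA or Kruskal-Wallis. Assumed, because the article gives no values: SD of 1 at each time, equal within-patient correlation ρ of 0.3, 0.5 or 0.7, normal data, nothing missing.

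**2. The plan's own figure.** With a standardised change of 0.8, a two-sided paired t-test needs n = 15 for 80% power, and 15/(1 − 0.25) = 20 with 25% dropout. A three-group 1-way ANOVA with f = 0.8 needs 19 observations, or 21 with equal groups. So 20 can be reached in more than one way. The article does not say which was used, and nothing below depends on it.

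**3. Scenario.** No change at week 8 and a standardised paired change of 0.8 at month 6 only. The SD of a within-patient difference is √(2(1 − ρ)), so the mean shift at month 6 is d = 0.8·√(2(1 − ρ)):
- ρ = 0.3: d = 0.8·√1.4 = 0.947
- ρ = 0.5: d = 0.8·√1.0 = 0.800
- ρ = 0.7: d = 0.8·√0.6 = 0.620

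**4. Chance of P < .05 by simulation, n = 20.**

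| ρ | Planned 1-way ANOVA | Repeated-measures ANOVA | Paired t, preoperative vs week 8 |
|---|---|---|---|
| 0.3 | 89% | about 95% | about 5% |
| 0.5 | 75% | about 95% | about 5% |
| 0.7 | 40% | about 95% | about 5% |

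**5. Closed-form check of the repeated-measures column.** For means (0, 0, d), the noncentrality is λ = n·(2/3)·d²/(1 − ρ). Since d² = 0.64·2·(1 − ρ), ρ cancels: λ = 20·(2/3)·1.28 = 17.07. On 2 and 38 degrees of freedom this gives power of about 95%, as simulated.

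**6. Sensitivity to scaling.** If the month-6 shift is instead held at 0.8 of the between-patient SD, with ρ from 0 to 0.7, the planned ANOVA rejects in 72–78% of trials and Kruskal-Wallis in 69–74%. The paired week-8 test stays at about 5%.

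**7. The omnibus P cannot tell the patterns apart.** A true gain at week 8 kept at month 6, means (0, d, d), has the same spread of means as (0, 0, d). The planned ANOVA therefore rejects equally often: 89%, 75% and 40%. This follows from the symmetry of the test, not from the assumed values.

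**8. The named contrast.** At a standardised paired change of 0.8 at week 8, the two-sided paired t-test has 92.4% power with n = 20 and 82.1% with n = 15.

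**The case against.** **No false claim is planned.** A reader might infer that a significant omnibus result would be reported as success at week 8. The article does not say so. It states a significance level but no success rule, and it promises means or medians at each time, so a flat week 8 beside a higher month 6 would be visible. This objection stands. The risk is that the P value answers a different question and is misread.

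**Worsening.** A reader might also infer that the omnibus test is specially at fault because it can be significant when week 8 is worse. It can, but so can any two-sided test. With week 8 worse by a standardised 0.8, the paired preoperative-to-week-8 test rejects in about 92% of trials, against 40–89% for the planned ANOVA. What the named contrast adds is an estimate with a sign and an interval for the right comparison.

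**Sample size.** It is tempting to say that 20 was computed for a different test. The article names neither test nor type of effect size, so that would be an inference.

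**Detail left to an analysis plan.** A contrast could be set out there. But the article does not leave the primary test open. It names the test repeatedly, and the named test does not match the endpoint. Extending the Tukey comparisons to 2MWD would largely expose the feared case, since with change only at month 6 Tukey rejects week 8 versus preoperative in under 1% of trials. It would still leave three comparisons with none named as primary.

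**Exploratory design.** Limitations says that improvement cannot be attributed to HAL without a control group and that randomised trials are needed. This stands and lowers the stakes. Ordinary recovery affects week 8 as well as month 6.

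**Conclusion.** The mismatch holds: the endpoint is week 8, and the stated primary test is an omnibus test over three times that includes month 6, with no primary contrast. With no week-8 change and a standardised paired change of 0.8 at month 6, the planned ANOVA is significant in 89% to 40% of trials as the correlation rises from 0.3 to 0.7, against about 5% for a test of week 8 itself. Changing to a repeated-measures ANOVA does not help, since it rejects in about 95%. This point is therefore separate from whether the three times may be treated as independent groups.

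The percentages rest on assumed correlations, an assumed month-6 effect and complete data. The mismatch itself rests only on the text. The article supports neither a charge that success would be claimed wrongly nor one that the sample size belongs to another test. Given the single-arm exploratory design, this is a should-fix point.

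**What to change.** Name one primary analysis in Statistical Analysis, and repeat it in the Abstract and in Planned Outcomes and Statistical Analysis: the within-patient change in 2MWD from preoperative to week 8. Choose one method in advance: the week-8 contrast of a repeated-measures model, a paired t-test or a Wilcoxon signed-rank test. Test it two-sided at 5%, report the estimate, its sign and its 95% CI, and state that only a positive change counts as improvement. List preoperative versus month 6 and week 8 versus month 6 as secondary, and keep any three-time omnibus test as supportive.

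The cost is one sentence of text, settled before the data are analysed. No visits, measurements or patients are added. If the stated effect size of 0.8 is read as a standardised paired change, power is 92.4% with all 20 patients and still 82.1% with 15.

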**Objective:**

This study aims to evaluate the impact of neurorehabilitation using the Hybrid Assistive Limb (HAL) for Medical Use Lower Limb Type, developed by Japan's Tsukuba University and the robotics company Cyberdyne, on gait acquisition, improvement in activities of daily living (ADL), and enhancement of quality of life (QOL) in patients with lower limb amputation, and assess the effectiveness of early HAL-assisted gait training before and after amputation.

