Furthermore, for Barthel Index (BI), Functional Independence Measure (FIM), Frenchay Activities Index (FAI), SF-36, Health Utilities Index, EQ-5D-5L (quality-adjusted life years), long-term care insurance certification level, General Self-Efficacy Scale, and WHODAS 2.0, the mean (SD) [or median (IQR)] will be calculated. Comparisons between preoperative, postintervention, and 6-month postoperative outcomes will be performed using a 1-way ANOVA or the Kruskal-Wallis test, with multiple comparisons conducted using the Tukey method (or Steel-Dwass test). A 2-sided significance level of 5% and a 95% CI will be calculated. The same analysis will be conducted using the PPS as a secondary approach.

The primary efficacy analysis will be conducted using the FAS, which includes all participants who received at least one session of HAL-assisted gait training and have at least one postintervention efficacy observation. Participants who are found to violate key eligibility criteria will be excluded from the FAS.

A secondary analysis will be performed using the PPS, which is a subset of the FAS consisting of participants who completed HAL training (5 days per week, 30 minutes per session) without any major protocol deviations and for whom the primary outcome data are available.

For missing data, a descriptive analysis will first be conducted to assess the pattern and mechanism of missingness. If the data are judged to be missing at random, multiple imputation using chained equations will be applied to handle missing values in the primary outcomes. Additionally, sensitivity analyses will be performed by comparing results between complete-case and imputed datasets to evaluate the robustness of the findings.

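### Secondary outcomes are compared across visits with an independent-groups test and no stated missing-data method, so month-6 changes could be shifted if weaker patients are lost

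*Protocol article*

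**What the plan says.** Methods, Statistical Analysis, sets the rule for missing data. First "a descriptive analysis will first be conducted to assess the pattern and mechanism of missingness". The second step is conditional on a judgement that values are missing at random, and its scope is explicit: "multiple imputation using chained equations will be applied to handle missing values in the primary outcomes". Results, Planned Outcomes and Statistical Analysis, repeats the same scope: "multiple imputation will be applied to the primary outcomes". Both sections add a robustness check; in Methods the wording is "sensitivity analyses will be performed by comparing results between complete-case and imputed datasets".

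On the analysis set, Statistical Analysis says "For secondary evaluation items, analysis will also be conducted using the FAS population". A patient enters the FAS after one HAL session and a single later efficacy observation, so a complete set of visits is not required.

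The same section names 21 secondary variables: 12 on physical function (four of them gait parameters) and 9 on activity and participation. All are compared between the preoperative, postintervention and 6-month visits by one-way ANOVA or Kruskal-Wallis, with Tukey or Steel-Dwass multiple comparisons and 95% CIs.

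The Abstract's objective includes "improvement in activities of daily living (ADL), and enhancement of quality of life (QOL) in patients with lower limb amputation". The primary outcome is the 2-minute walking distance, so ADL and QOL are answered only by secondary outcomes.

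**The concern.** One-way ANOVA and Kruskal-Wallis treat the three visits as three separate groups of people. They discard the within-patient pairing and accept a different number of patients at each visit. No handling of missing secondary data is stated, so the straightforward way to run these tests is to use whoever was measured at each visit. The preoperative mean could then describe the whole FAS, and the month-6 mean only those who returned.

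The article gives reasons to expect some loss, possibly related to function. The discontinuation criteria under Interventions include worsening disease, exacerbated comorbidity, adverse events and low device use after complications. The Withdrawal column of Table 2 marks only adverse event monitoring. Patients stay in hospital until the week-8 evaluation, so month 6 is the assessment after discharge. Sample Size anticipates dropouts.

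If weaker patients are the ones missing at month 6, part of an apparent gain in ADL, QOL or function would reflect who came back. With a single arm, no control group is present to show the same distortion.

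**Working it through.** The article gives no loss rate, SD or between-visit correlation, so it has no figure on this point to reproduce.

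**Inputs from the article:** 20 patients, three visits, one-way ANOVA, two-sided 5% level, FAS entry on one later observation.

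**Assumptions:** no true change; unit SD, scored so that higher is better; correlation ρ between visits of 0.5 to 0.8; 2, 4 or 6 of 20 patients (10%, 20%, 30%) missing at month 6 only.

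**1. What ignoring the pairing costs with complete data.** The standard error of a difference between two visit means is √(2/20) = 0.316 SD if the visits are treated as independent. With pairing it is √(2(1−ρ)/20), which is √0.05 = 0.224 SD at ρ = 0.5 and √0.02 = 0.141 SD at ρ = 0.8.

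**2. Expected shift in the unpaired difference.** Let m be the mean preoperative value, in SD units, of the patients who remain; the full-group mean is 0. If loss depends on the preoperative value, the expected month-6 mean of those remaining is ρ × m, so the spurious change is ρ × m. If the 4 lowest of 20 are lost, m = 0.333:
- ρ = 0.5: 0.5 × 0.333 = 0.167
- ρ = 0.7: 0.7 × 0.333 = 0.233
- ρ = 0.8: 0.8 × 0.333 = 0.266

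A simulation of 20,000 trials per setting gave 0.166, 0.233 and 0.264.

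**3. Range of the shift (SD, month 6 minus preoperative, simulated over ρ = 0.5 to 0.8).**

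| Missing at month 6 | Lowest preoperative values lost | Loss partly related to preoperative value | Loss unrelated to function |
|---|---|---|---|
| 10% | 0.09 to 0.15 | 0.07 to 0.10 | 0.00 |
| 20% | 0.17 to 0.26 | 0.12 to 0.19 | 0.00 |
| 30% | 0.24 to 0.38 | 0.17 to 0.27 | 0.00 |

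A second set of simulations (6,000 trials per setting) let loss depend on the week-8 value, with 15-25% lost, odds ratio 2 to 4.5 per SD and ρ from 0.4 to 0.8. It gave 0.04 to 0.22 SD. If exactly the worst 3 to 5 of 20 at week 8 are lost, the shift runs from 0.258 × 0.4 = 0.10 to 0.405 × 0.8 = 0.32 SD. Taken together, the function-related settings span 0.04 to 0.38 SD.

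**4. False positives.** In the 20,000-trial simulations the one-way ANOVA rejected in at most 2.3% of null trials, and in 0.0 to 0.5% with no data missing. Ignoring the pairing makes it conservative, which outweighs the shift. Kruskal-Wallis and the multiple comparison procedures were not simulated.

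**5. Alternatives on the same data.**
- An estimate using all patients and conditioning on the preoperative value was within 0.005 SD of zero in every setting of the table. In the week-8 settings, a maximum likelihood estimate from all visits was within 0.007 SD of zero.
- Restricting to patients with both visits gives (ρ − 1) × m when loss depends on the preoperative value. With 4 lost this is −0.5 × 0.333 = −0.167 at ρ = 0.5 and −0.2 × 0.333 = −0.067 at ρ = 0.8. Across the function-related settings of the table the simulated range is −0.03 to −0.24 SD. Pairing completers therefore replaces one bias with another of opposite sign.

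**The case against.** The strongest reply is that this is a condensed article. It prescribes neither an available-case nor a complete-case analysis of secondary outcomes, and such detail is commonly left to the full protocol or SAP. Planned Outcomes and Statistical Analysis also says that secondary outcomes follow a similar approach to the primary one, which might be meant to include missing data. Neither the review of missingness nor the complete-case comparison is expressly limited to the primary outcome; for the comparison that limit is only the natural reading in context. Month 6 provides secondary, longer-term data, the study calls itself exploratory, and the shifts are modest beside a standard error of 1/√20 = 0.22 SD for a single visit mean.

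Much of this stands. A reader might infer that every secondary outcome will be compared on different patients, that loss of weak patients will appear as improvement, or that spurious significance will follow. The article supports none of these. The first needs missing data analysed as available, and the second needs loss that depends on function. The third is contradicted by the ANOVA rejection rates. Inpatient care up to the week-8 evaluation also confines the problem mainly to month 6.

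The reply does not remove what is stated. The independent-groups test is named for the secondary outcomes, the scope of imputation is written out twice, and the FAS admits incomplete patients. Silence alone would not be a finding; the stated test on that analysis set is one.

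**Conclusion.** The point holds in conditional form. The named test ignores within-patient pairing whether or not data are missing. Combined with an FAS that admits missing visits and imputation named only for the primary outcome, it leaves the month-6 change in ADL, QOL and function open to a shift toward improvement of about 0.04 to 0.38 SD. That range rests on assumed function-related loss of 10-30% and correlations of 0.4 to 0.8. It is zero if loss is unrelated to function, and the article does not say which to expect. The effect is on the estimate and its CI, not on an inflated false-positive rate. The plan should be changed, but the point does not invalidate the trial. The same independent-groups test is planned for the primary outcome, so extending imputation alone would leave that defect in place.

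**What to change.** In Statistical Analysis and in Planned Outcomes and Statistical Analysis:

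- For scale and continuous secondary outcomes, replace the independent-groups test with a likelihood-based repeated-measures mixed model using every available visit. Report within-patient contrasts (week 8 and month 6 against preoperative) with 95% CIs.
- State missing at random as the assumption of that model for the secondary outcomes. The model does not protect against loss that depends on unobserved month-6 values.
- For ordinal items such as the care insurance level, use a paired or repeated-measures ordinal method, report the n for each contrast, and note that an analysis of paired completers may still be biased.
- Do not extend chained-equation imputation to all 21 secondary variables; 20 patients give weak support for it, and the mixed model already uses the incomplete records.
- Do not substitute a classical repeated-measures ANOVA, which drops every patient with a missing visit.

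The cost is revised wording, slightly more programming and reliance on the missing-at-random assumption. No new patients or data are needed.
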